### Recruitment

Patients will be recruited from hospitals in various European countries. Up until now, hospitals in Denmark, UK, Finland, France, Italy and Sweden have agreed to participate. During the inclusion period, it will remain possible for other centres to join. To achieve adequate participant enrolment, we have minimalised the exclusion criteria. Collaboration within ERNICA should make patient accrual achievable despite the rarity of the disease.

### Randomisation, blinding and treatment allocation

Randomisation will be conducted via ALEA (FormsVision B.V./ALEA Clinica B.V.), a validated software program. To achieve equal distribution of the intervention among the participating sites, block randomisation stratified per centre will be carried out. The software was prepared by an independent statistician who is not otherwise involved in the study. After inclusion, the local PI will enter the patient in ALEA and will thereupon receive an email stating the allocated treatment.

Randomisation will be blinded for the radiologist who will review all oesophagrams. The control group will not receive sham treatment. The steroid that will be used, Kenacort-A 10 (see further), is a white suspension, which complicates creating a placebo. Adding excipients to normal saline is undesirable, considering the unknown effect on the healing process of the stricture. Moreover, it is deemed undesirable to inject an infant with a fluid with an unknown effect.

### Investigational product

The intervention will be a one-time endoscopic injection of 0.25 mL Kenacort-A 10 (Bristol-Myers Squibb BV, Utrecht, the Netherlands) in each quadrant of the stricture prior to the third endoscopic dilatation. Thus, in total, 1 mL (10 mg/mL TAC, equals 12.5 mg prednisone) will be injected. During the study period, none of the patients will receive a second injection.

Kenacort-A 10 will be prepared, labelled and distributed by the trial pharmacy of the coordinating hospital. It will be delivered to the local pharmacies by courier, and the local pharmacy will deliver it to the operation room when needed. After the trial, a specific procedure for destruction of the remaining drugs is not needed; they can be disposed of locally.

### Patient timeline

Figure 1 presents a flowchart for this study and the study procedures. The treating physician will decide on a third dilatation on the basis of the clinical signs of dysphagia and the findings on the oesophagram (thoracic X-ray with contrast, anterior–posterior and lateral). Clinical signs of dysphagia are defined as the inability to be fed age appropriately. Findings on the oesophagram indicating a stricture are defined as a significant narrowing of the lumen, seen as a waist in the contrast on the X-ray. The treating physician can be a paediatric surgeon or a paediatric gastroenterologist, depending on the local agreements in the different countries. After parental informed consent, the patient will be included and randomised to one of the study arms.

**Figure 1 F1:**
[figure not shown]
Flowchart of the study design. Bold with underline indicates study procedures; the rest is standard of care. AP, anterior–posterior; iPCQ, iMTA Productivity Cost Questionnaire; MFS, Montreal Feeding Scale; OA, oesophageal atresia.

Prior to the balloon dilatation, an endoscopic needle (DVI-23-MH varices injector or equivalent) is prefilled with 1 mL Kenacort-A 10 and passed through the endoscope. Under direct vision, 0.25 mL will be injected in each of the four quadrants of the circular stricture. After the injection needle has been retracted from the working channel and good visualisation has been re-established, balloon dilatation will be performed up to the desired diameter. The balloon will remain insufflated for 1 min.

During a follow-up period of 6 months, patients will not receive any (additional) steroid injections, only balloon dilatations if needed. Meaning, patients in the steroid group will only receive one injection, and patients in the control group will receive no injections at all. After the study period has ended, treatment is again free of choice.

Two to 3 weeks after the dilatation procedure, a second oesophagram will be made in children in both study groups. All oesophagrams will be reviewed by one specialised paediatric radiologist of the coordinating hospital, who will determine the oesophageal diameter and stricture length. Earlier studies have proven that these measurements can be obtained from an oesophagram.^24^ The parents will be informed about the results and the normal standard of care will be continued.

Each patient will be followed up for 6 months after the third dilatation, with recording of possible side effects, complications and additional dilatations. Length and weight will be measured at 2–3 weeks, 3 and 6 months after the third dilatation. In the context of the cost-effectiveness analysis, the parents will be asked to fill out a modified version of the iMTA Productivity Cost Questionnaire (iPCQ)^25^ at 3 months after the third dilatation.

At evaluation at 6 months, we will collect a scalp hair sample from the child to determine long-term cortisone and cortisol levels.^26 27^ The hair locks will be stored for final batch analysis. Lastly, the parents will be asked to fill out the Montreal Feeding Scale (MFS)^28–30^ and again the iPCQ. After this, the study period will end.

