**Trial registration numbers:**

2018-002863-24 and NTR7726/NL7484.

Strengths and limitations of this studyThis is the first prospective study investigating the effectiveness of intralesional steroid injection combined with endoscopic dilatation for the treatment of recurrent oesophageal strictures in children operated on for oesophageal atresia (OA).The determination of long-term cortisol levels over a period of 3 months will give objective information on possible systemic effects of intralesional steroid injection in children with OA.Besides the effectiveness and safety of intralesional steroid injection, cost-effectiveness of this treatment will be evaluated.The rarity of the disease makes patient recruitment challenging.

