### Participants

OA can be a very heterogeneous disease. About 90% of the children with OA has type C.^5 23^ In order to make the two treatment groups as equal as possible, only children with OA type C who underwent surgery with primary anastomosis within the first days of life and who developed a recurrent oesophageal stricture will be eligible. Children will be included if they are ≥3 months old at the time of the intervention and in need of a third dilatation. Written parental informed consent will be obtained by the local principal investigator (PI) or another member of the local research team. Exclusion criteria are lack of parental consent or an impossibility—known from previous dilatations—to use an endoscope with a large enough diameter working channel to pass the endoscopic injector.

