### Outcome parameters

The primary outcome parameter is the total number of dilatations required per patient with a 28-day interval between the dilatations during the study period of 6 months, which is defined as the period from the day of the third dilatation until 6 months later.

The secondary outcome parameters are as follows:

Total number of dilatations within the study period, regardless of the interval.Interval (in weeks) between the start of the study and the last dilatation procedure within the study period.Scores on the MFS.The change in maximal luminal diameter after the third dilatation relative to the diameter before the third dilatation: relative change in luminal diameter=(maximal diameter after–maximal diameter before)/maximal diameter before. The diameter will be measured at the narrowest point of the oesophagus.The change in the length of the oesophageal stricture after the third dilatation relative to the length before the third dilatation: relative change in stricture length=(stricture length after–stricture length before)/stricture length before. The length will be measured between the two points where the oesophageal diameter starts narrowing.The use of comedication (eg, antacids) during the study period.The mean hair cortisol levels in the first 3 months after the third dilatation. Cortisol levels will be adjusted for age and sex.Delta length SD scores (SDSs) and delta weight SDS between the third dilatation (intervention) and 3 and 6 months after the third dilatation.Total costs of the treatment, including medical and non-medical costs.Incremental costs per refractory stricture prevented and incremental costs per additional dysphagia-free patient.

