### Data collection

All participating centres are familiar with the procedure of injecting Kenacort-A 10 in the lesion via an injection needle through the endoscope. However, to guarantee equality of the intervention, the relevant practitioners in all centres will be trained by the PI of the trial. Radiological interobserver variability will be avoided by having all oesophagrams reviewed by one radiologist.

The internationally validated MFS^28–30^ will be used to measure dysphagia. The MFS has often been used in previous research in children with OA. The scalp hair sample will be taken from the posterior vertex; cortisol levels will be determined with the liquid chromatography–tandem mass spectrometry method for quantification of steroids.^26^

The cost-effectiveness analysis will follow established methods for economic evaluations and costing studies in healthcare.^31 32^ Both medical and non-medical costs will be collected. Medical costs will include costs of surgeries (dilatations), steroid injections, hospital days (on the ward or the intensive care unit), medication (such as analgesics) and diagnostic radiography. Costs of healthcare provided by others than the participating centres (such as other hospitals or general practitioners) will be ignored in this study, as these are unlikely to be affected by the intervention. Non-medical costs will include costs of special diets, costs related to hospital visits and productivity losses related to both paid and unpaid works. The non-medical costs will be measured using the iPCQ,^25^ supplemented with additional questions on costs of special diets and costs related to the child’s hospitalisation. The original iPCQ questions are validated in English. The complete questionnaire including the additional questions will be translated to the languages required for this trial using the forward–backward translation method, as will the MFS for the languages it has not been validated for.

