### Statistical analysis

Since a standardised treatment protocol will be adopted in all centres, statistical adjustment for centre effects is considered unnecessary.

The primary outcome parameter will be analysed with a linear-by-linear χ^2^ association test. The total number of dilatations required with a 28-day interval (ie, refractory strictures) within the study period of 6 months per patient will be categorised and compared between treatment groups. In case of death during the follow-up period, the outcome will be set to the highest (ie, most severe) category. In case of drop-out during the follow-up period due to other causes (eg, emigration and withdrawal), the subject will be excluded from the study.

The analyses for the secondary study parameters are as follows:

The total number of dilatations required within the study period (regardless of the interval, ie, all strictures) will be categorised and compared between treatment groups with a linear-by-linear χ^2^ association test.The interval (in weeks) until the patient is dysphagia-free will be compared between groups with the log-rank test and with Cox proportional hazards regression, with adjustment for treatment group and factors such as age, sex, diagnostic information and described risk factors for stricture formation like anastomotic leaking and thoracoscopic repair.^5^ Patients who do not become dysphagia-free during follow-up are treated as censored at the end of the follow-up period.The scores on the MFS (reflecting the level of dysphagia and the eating behaviour) will be compared between study groups with a Mann-Whitney test.The relative change in the oesophageal diameter and that in the length of the oesophageal stricture will be compared between study groups with an analysis of covariance model. The dependent variables in this model will be the log-transformed oesophageal diameter and length after the third dilatation, and the independent variables will be the treatment group and the log-transformed oesophageal diameter and length before third dilatation.The effect of comedication on the primary study outcome will be assessed using a stratified Mann-Whitney test with stratification for the treatment group.The mean cortisol level over the first 3 months after the third dilatation will be compared between study groups with a linear regression model with adjustment for age and sex.

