No missing data are expected for the independent variables in the analysis of covariance models and the Cox proportional hazards regression models. In case of missing data for any of the outcomes, a complete case analysis (ie, exclusion of the subjects who dropped out during the follow-up period) will be performed for the corresponding outcome.

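### The only hair sample is cut at 6 months for a cortisol outcome that covers the first 3 months, which exposes that outcome to avoidable loss and dating error

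*Protocol article*

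**What the plan says.** All places are in the protocol article.

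- **Sampling time (Patient timeline):** "At evaluation at 6 months, we will collect a scalp hair sample from the child to determine long-term cortisone and cortisol levels". No other hair sample is described.
- **Outcome (Outcome parameters):** "The mean hair cortisol levels in the first 3 months after the third dilatation", adjusted for age and sex.
- **Analysis (Statistical analysis):** "The mean cortisol level over the first 3 months after the third dilatation will be compared between study groups with a linear regression model", again adjusted for age and sex.
- **Purpose (strengths and limitations list):** "The determination of long-term cortisol levels over a period of 3 months will give objective information on possible systemic effects".
- **Sampling site (Data collection):** "The scalp hair sample will be taken from the posterior vertex". The assay is named as well.
- **Age (Participants):** "Children will be included if they are ≥3 months old at the time of the intervention". No upper age limit is given.
- **Existing visits (Patient timeline):** "Length and weight will be measured at 2–3 weeks, 3 and 6 months after the third dilatation".
- **Missing outcomes (Statistical analysis, last paragraph):** "In case of missing data for any of the outcomes, a complete case analysis" is performed for the outcome concerned.

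**The concern.** The sample is taken three months after the outcome window has closed. Hair grows from the scalp outwards, so at 6 months the hair nearest the scalp was formed most recently and the wanted hair is the older, outer part of the strand. No outcome or analysis uses cortisol from months 3 to 6, so the wait gains nothing that the plan evaluates.

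At stake is the only biochemical measure of systemic steroid exposure that the article describes. Adrenal suppression is among the potential complications listed under Benefits and risk assessment, and systemic effects are a stated secondary objective. If the outer part of the strand is missing, the child drops out of this analysis. If the segment is placed wrongly, the value mixes in months that the outcome does not cover, including months before the injection.

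**Working it through.** The plan gives no computed figure on this point, so there is none to reproduce. The check is one of position and timing.

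**Inputs.** From the article: cut at month 6; window months 0 to 3; existing evaluation at month 3; age at least 3 months at the intervention; 52 children per group (Sample size calculation). Not in the article, hence assumed: growth g between 0.5 and 1.25 cm per month, and the share of children with usable hair. Any delay between hair forming and emerging from the scalp is ignored.

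**1. Where the window lies.** Hair formed at study month t lies (T − t) × g cm from the scalp when cut at month T. For t from 0 to 3 this gives 3g to 6g at T = 6, and 0 to 3g at T = 3.

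| g (cm/month) | Cut at month 6 | Cut at month 3 |
|---|---|---|
| 0.5 | 1.5–3.0 cm | 0–1.5 cm |
| 0.75 | 2.25–4.5 cm | 0–2.25 cm |
| 1.0 | 3.0–6.0 cm | 0–3.0 cm |
| 1.25 | 3.75–7.5 cm | 0–3.75 cm |

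The strand length needed for the whole window is twice as great at month 6, whatever g is.

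**2. What that does to availability.** The piece at 3g to 6g at month 6 is the same piece of hair that lay at 0 to 3g at month 3. Every child who still has it at month 6 therefore had it at month 3. The reverse fails if the hair was cut or shed, or the child left the study, in between. The later date can lose usable samples but cannot add any for this window.

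**3. What that does to dating.** Suppose the laboratory assumes a growth rate a while the true rate is g.

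- Cut at month 6, segment 3a to 6a: it covers months 6 − 6a/g to 6 − 3a/g. The outer end is off by 6(1 − a/g) months and the inner end by 3(1 − a/g).
- Cut at month 3, segment 0 to 3a: it covers months 3 − 3a/g to 3. The outer end is off by 3(1 − a/g) months and the inner end by nothing.

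The outer error doubles, and an inner error appears. With a = 1.0 as an illustration:

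| True g | Months covered, cut at 6 | Share of segment in window | Months covered, cut at 3 | Share of segment in window |
|---|---|---|---|---|
| 0.5 | −6 to 0 | 0% | −3 to 3 | 3/6 = 50% |
| 0.75 | −2 to 2 | 2/4 = 50% | −1 to 3 | 3/4 = 75% |
| 1.0 | 0 to 3 | 100% | 0 to 3 | 100% |
| 1.25 | 1.2 to 3.6 | 1.8/2.4 = 75% | 0.6 to 3 | 100% |

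**4. What lost samples would cost.** For two means, the standardised difference detectable with 80% power at two-sided 0.05 is √(2/n) × (1.96 + 0.84).

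| Usable share (assumed) | n per group | Detectable difference |
|---|---|---|
| 100% | 52 | 0.55 |
| 75% | 39 | 0.63 |
| 50% | 26 | 0.78 |
| 25% | 13 | 1.10 |

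This shows how precision depends on the usable share. It does not forecast that share. It also ignores any gain from adjusting for age and sex.

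**The case against.** The strongest reply is that nothing here is inconsistent. Hair is a retrospective record, the outcome and its regression both name the 0–3 month window, and no sentence says that the hair nearest the scalp will be assayed at 6 months. Segment length, minimum length and a rule for short hair may well stand in the full protocol, a laboratory manual or the analysis plan, none of which is shown. This stands: the missing segment rule is no finding, and a reader who infers a contradiction goes too far. What remains is the choice of sampling date against the outcome window, and the article itself fixes both.

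A second reply is that doubling the required length does not double the difficulty, because the hair has three more months to grow. This also stands. Slow growth alone does not remove the segment, and at 3 months the youngest children, then about 6 months old, have less hair in total. But the relevant piece is the same hair on both dates, so the wait offers no compensating gain.

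A third reply is that losses would probably be similar in the two randomised arms and that the regression adjusts for age and sex. The documents show no mechanism for bias between arms. The foreseeable cost is lost precision and blurred timing in one secondary outcome.

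**Conclusion.** The point holds as a cheap improvement to one secondary outcome. The 6-month cut moves the target window from 0–3g cm to 3g–6g cm from the scalp. It thereby exposes the cortisol measure to avoidable loss from cutting, shedding or dropout between months 3 and 6, and to misdating at both ends of the segment. The doubling of the required length, and of the outer dating error, holds for any steady growth rate. The centimetre figures rest on the assumed 0.5 to 1.25 cm per month, and the detectable differences on assumed usable shares.

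A reader might infer three stronger things that the documents do not support:

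- **That most samples will be missing or show the wrong months.** This needs hair length and growth in these children, which are not given. About 9 months at sampling is the youngest possible age, not the typical one.
- **That the question of systemic effects goes unanswered.** Changes in length and weight SD scores at 3 and 6 months and the recording of adverse events remain. Only the cortisol part is at risk.
- **That any adrenal effect will be over by months 3 to 6.** The article calls the product slow-release and gives no duration.

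**What to change.** Move the hair sample in Patient timeline from the 6-month to the existing 3-month evaluation, and assay the segment nearest the scalp that covers the time since the third dilatation. Figure 1 (not reproduced in the text at hand) needs the same change if it shows the sample. The cortisol entries in Outcome parameters and Statistical analysis can stay as they are.

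One sentence should go with it. Statistical analysis excludes children who drop out, in one place from the study and in another for the outcome concerned. A child who leaves after month 3 but has given hair contributes to the cortisol analysis only under the second reading, so the amendment should say which applies.

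The cost is a small amendment, for which Ethics and dissemination already gives the route. The sample is moved rather than added, so there is no extra visit or procedure. At publication, Trial status reports that the first patient is included and that six sites are awaiting approval, so few children would be affected by the change. The downside is that cortisol information for months 3 to 6 is given up, which no stated outcome uses.

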### Outcome parameters

The primary outcome parameter is the total number of dilatations required per patient with a 28-day interval between the dilatations during the study period of 6 months, which is defined as the period from the day of the third dilatation until 6 months later.

The secondary outcome parameters are as follows:

Total number of dilatations within the study period, regardless of the interval.Interval (in weeks) between the start of the study and the last dilatation procedure within the study period.Scores on the MFS.The change in maximal luminal diameter after the third dilatation relative to the diameter before the third dilatation: relative change in luminal diameter=(maximal diameter after–maximal diameter before)/maximal diameter before. The diameter will be measured at the narrowest point of the oesophagus.The change in the length of the oesophageal stricture after the third dilatation relative to the length before the third dilatation: relative change in stricture length=(stricture length after–stricture length before)/stricture length before. The length will be measured between the two points where the oesophageal diameter starts narrowing.The use of comedication (eg, antacids) during the study period.The mean hair cortisol levels in the first 3 months after the third dilatation. Cortisol levels will be adjusted for age and sex.Delta length SD scores (SDSs) and delta weight SDS between the third dilatation (intervention) and 3 and 6 months after the third dilatation.Total costs of the treatment, including medical and non-medical costs.Incremental costs per refractory stricture prevented and incremental costs per additional dysphagia-free patient.

